## Abstract

**Background:** Given rising morbidity, mortality, and costs due to heart failure (HF), new approaches for prevention are needed. A quantitative risk-based strategy, in line with established guidelines for atherosclerotic cardiovascular disease prevention, may efficiently select patients most likely to benefit from intensification of preventive care, but a risk-based strategy has not yet been applied to HF prevention.

**Methods and Results:** The Feasibility of the Implementation of Tools for Heart Failure Risk Prediction (FIT-HF) pilot study will enroll 100 participants free of cardiovascular disease who receive primary care at a single integrated health system and have a 10-year predicted risk of HF of ≥5% based on the previously validated Pooled Cohort equations to Prevent Heart Failure. All participants will complete a health and lifestyle questionnaire and undergo cardiac biomarker (B-type natriuretic peptide [BNP] and high-sensitivity cardiac troponin I [hs-cTn]) and echocardiography screening at baseline and 1-year follow-up. Participants will be randomized 1:1 to either a pharmacist-led intervention or usual care for 1 year. Participants in the intervention arm will undergo consultation with a pharmacist operating under a collaborative practice agreement with a supervising cardiologist. The pharmacist will perform lifestyle counseling and recommend initiation or intensification of therapies to optimize risk factor (hypertension, diabetes, and cholesterol) management according to the most recent clinical practice guidelines. The primary outcome is change in BNP at 1-year, and secondary and exploratory outcomes include changes in hs-cTn, risk factor levels, and cardiac mechanics at follow-up. Feasibility will be examined by monitoring retention rates.

**Conclusions:** The FIT-HF pilot study will offer insight into the feasibility of a strategy of quantitative risk-based enrollment into a pharmacist-led prevention program to reduce heart failure risk.

**Clinical Trial Registration:**
https://clinicaltrials.gov/ct2/show/NCT04684264

## Background

Although overall cardiovascular disease mortality has declined 3-fold over the past five decades (1), this has been largely driven by improvement in ischemic heart disease mortality rates (2). Advances in the prevention of ischemic heart disease have now been offset by increasing mortality related to heart failure (HF), resulting in stagnation in overall cardiovascular disease mortality rates since 2011 (3). HF affects an estimated six million American adults, a prevalence which is expected to increase nearly 50% by 2030, and is responsible for ~1 million hospitalizations and two million physician office visits annually (4).

Given the large and rising morbidity, mortality, and costs of HF, evidence-based and generalizable prevention strategies, which currently exist for atherosclerotic cardiovascular disease (ASCVD) (5) but not HF, are needed. Two important questions in the design of a potential HF prevention strategy include (1) how to assess patients' individual risk for HF and (2) how to intensify prevention efforts in patients identified as high risk.

### Heart Failure Risk Assessment

The 2017 focused update of the American College of Cardiology/American Heart Association (ACC/AHA) Guideline for the Management of HF highlights the potential role of natriuretic peptide biomarker screening, followed by team-based care, in those at risk for HF (6). This guideline recommendation was informed by two randomized controlled trials, the STOP-HF trial and the PONTIAC trial, which demonstrated that referral to collaborative cardiology care based on natriuretic peptide value cutoffs in patients at high cardiovascular risk may prevent HF (7, 8). However, in STOP-HF, only 27% of patients had a BNP > 50 pg/mL, the threshold for referral to cardiology. In addition, a risk factor-based approach that treats all risk factors equally (as in STOP-HF) or requires the presence of a particular risk factor such as diabetes (as in PONTIAC) may miss some patients at high risk due to elevations below treatment thresholds in multiple risk factors and may over-sample some patients at low risk, such as younger adults with a single risk factor. In contrast, multivariable risk prediction equations for HF, such as the Pooled Cohort equations to Prevent HF (PCP-HF) (9), that incorporate clinical measures readily available in primary care settings may improve identification of those at risk for HF who may merit more intensive prevention strategies.

### Pharmacist-led Intensification of Preventive Care

Efforts to intensify preventive care have been implemented with a variety of healthcare and non-healthcare team members such as pharmacists (10, 11), nurses (12, 13), and community healthcare workers (14), and through leveraging digital tools such as web-based portals (15) and remote monitoring (16). Several prior reports suggest a potential benefit of involvement of these team members in strategies for hypertension or diabetes control (11, 13–16); for example, a trial of a nurse-led clinic for patients with diabetes showed that, at 1 year, 37.2% of patients in the intervention met their cholesterol and/or blood pressure target compared with 30.7% of patients receiving usual care (OR 1.37 [95% CI: 1.11, 1.69]) (13). Pharmacist-led interventions have unique advantages, as pharmacists are experts in the medications that achieve core targets of primary prevention, including blood pressure, glucose, and lipid lowering; pharmacists are well-positioned to counsel patients about sodium-glucose cotransporter-2 (SGLT-2) inhibitors, one of the most promising recent medications for the prevention of heart failure (17); and pharmacists may, under collaborative practice agreements with supervising physicians, directly prescribe and titrate medications for patients. In addition, pharmacists may be deployed in communities and have a potent effect on preventive care for underserved populations, as was recently demonstrated in a trial of a pharmacist-led intervention for blood pressure reduction in barbershops in predominantly Black communities (18).

### Rationale of Risk-Based Heart Failure Prevention

It would be neither feasible nor cost-effective to perform biomarker screening or intensify preventive efforts in the entire population. Risk-based prevention strategies, in which the intensity of prevention efforts are tailored to the predicted risk of disease based on a comprehensive risk factor profile, maximize the potential benefits of preventive strategies and are well-established in atherosclerotic cardiovascular disease (ASCVD) (19–21). However, a quantitative risk-based approach has not yet been applied to the primary prevention of heart failure and requires further investigation with regard to the feasibility and efficacy of such an approach. Therefore, in this report we describe the design of a pilot study of a pharmacist-led intervention program for risk-based prevention of HF, the Feasibility of the Implementation of Tools for Heart Failure Risk Prediction (FIT-HF) Study. The FIT-HF Study will enroll 100 patients free of any type of cardiovascular disease with a predicted 10-year risk of developing heart failure, based upon the PCP-HF, (9) of 5% or higher. Patients will undergo BNP, hs-cTn, and echocardiogram testing at baseline and will be randomized to a pharmacist-led intervention or usual care. Successful completion of this pilot study will demonstrate feasibility of the proposed strategy and generate preliminary data to support the design of a subsequent, well-powered trial evaluating clinical event outcomes.

## Study Design

### Eligible Study Population

The FIT-HF study will enroll 100 participants who receive primary care at a single integrated academic healthcare center, Northwestern Medicine. Eligible participants will be aged 30–79 years and have at least one internal medicine visit in the past year, at least two such visits in the past 5 years, and cholesterol and glucose levels measured within the past 5 years. In addition, using the most recently available data in the electronic health record (EHR), participants will have a predicted 10-year risk of developing HF of at least 5% based on the PCP-HF model (9). The variables in the PCP-HF model are age, sex, race, smoking, body mass index, systolic blood pressure, hypertension treatment, fasting glucose, diabetes treatment, total cholesterol, high density lipoprotein cholesterol, and QRS duration. Because real-world glucose measurements are often non-fasting, and QRS duration is not routinely clinically available, a version of the PCP-HF equations calibrated to random glucose values and excluding QRS duration will be used (22). The 5% cutoff of 10-year predicted HF risk represents approximately the top quintile of risk among US adults (23). Participants are ineligible if they have a history of cardiovascular disease (by EHR diagnosis code or self-report), signs or symptoms of HF, a current pregnancy, an estimated glomerular filtration rate <45 mL/min/1.73 m^2^ using the CKD-EPI (2009) formula either prior to or during the baseline exam, or stage three or four cancer. Detailed inclusion and exclusion criteria are available in the Supplementary Methods.

### Study Recruitment

Recruitment will be accomplished leveraging the robust Northwestern Medicine Enterprise Data Warehouse (NMEDW), which is a comprehensive and integrated repository of all clinical, administrative, and research data sources on the campus. Briefly, the NMEDW currently stores observations on more than 7.1 million distinct patients and is updated in real time with data elements from 142 separate sources, including electronic health records, pathology data from the hospital and research laboratories, biomarker data from research databases and research transactional data from the Northwestern Institutional Review Board and other institutional systems. The NMEDW-based algorithm has been customized to identify all patients meeting study eligibility criteria based on existing data in their electronic health record and automatically excludes patients who opted out of being contacted for research studies, thus allowing for targeted and highly efficient recruitment of patients. The baseline characteristics of patients in the recruitment report are listed in Table 1, which identified 13,059 potentially eligible patients with a mean (standard deviation) age of 66.6 (8.5) years. The time frame for full enrollment is 1 year, with the final participant expected to complete the protocol 2 years after the beginning of the study.

**Table 1 T1:** Baseline characteristics of patients potentially eligible for recruitment.

* **N** *	**13,059**
Age (years), mean (SD)	66.6 (8.5)
**Gender**, ***N*** **(%)**	
Female	6,040 (46.3%)
Male	7,019 (53.7%)
**Self-reported race**, ***N*** **(%)**	
White	8,832 (67.6%)
Black or African American	2,210 (16.9%)
Asian	450 (3.4%)
Other or Declined	1,567 (12.0%)
Body mass index (kg/m^2^), median (IQR)	29.7 (26.1, 34.6)
Systolic blood pressure (mmHg), mean (SD)	136.1 (17.2)
Diastolic blood pressure (mmHg), mean (SD)	78.3 (10.0)
Glucose (mg/dL), mean (SD)	116.3 (42.4)
Total cholesterol (mg/dL), mean (SD)	181.3 (40.5)
HDL cholesterol (mg/dL), mean (SD)	53.8 (15.7)
LDL cholesterol (mg/dL), mean (SD)	101.6 (36.3)
**Medication use**, ***N*** **(%)**	
Antihypertensive	10,594 (81.1%)
Antidiabetic	2,919 (22.4%)
Statin	8,132 (62.3%)
Current smoking, *N* (%)	1,180 (9.0%)
Estimated 10-year heart failure risk, median (IQR)	8.0% (6.2, 11.2)

### Study Protocol

A research coordinator will call patients listed in the recruitment report to confirm eligibility, describe the study, and ask if they are interested in participating. If so, the research coordinator will review study procedures over the phone and schedule a visit in the research clinic. Participants will be emailed a link to sign electronic consent (e-Consent) and complete a baseline health and lifestyle questionnaire. The e-Consent option will offer flexibility and minimize in-person time to decrease participant burden during and after the COVID-19 pandemic. The questionnaire is composed of previously validated questions from the World Health Organization, Multi-Ethnic Study of Atherosclerosis (MESA), and EuroQol. Participants who are unwilling or unable to complete these procedures online will be instructed to arrive 30 min before their scheduled visit in order to sign written consent and complete the questionnaire in person. After consent is obtained, participants will then be randomized in 1:1 fashion to intervention vs. usual care (Figure 1). The randomization table will be generated using random permuted blocks of sizes four and six by a statistician with no other involvement in the study.

**Figure 1 F1:**
[figure not shown]
Overview of the FIT-HF study. Participants will be recruited by invitation from the eligible study population using an electronic health record-based report. They will complete eConsent and questionnaires online and have biomarkers measured and echocardiograms performed at baseline and 1 year. In the interim, they will be randomized 1:1 to a pharmacist-led intervention or to usual care. HF represents heart failure; EDW Enterprise Data Warehouse. Created with BioRender.com.

All participants will undergo phlebotomy for measurement of BNP, hs-cTn, basic metabolic panel, lipid panel, and biorepository storage, and baseline echocardiography with Doppler measurements. All participants will also undergo measurement of vital signs and receive an educational packet of information from the Centers for Disease Control and Prevention and American Heart Association on signs and symptoms of HF and heart-healthy lifestyle.

Participants who are randomized to the intervention arm will receive a referral to the pharmacist-led intervention (supervised by an attending cardiologist), and have their first visit on the same day as the baseline testing. Two pharmacy residents will deliver the intervention under the supervision of an attending pharmacist. Residents have received standardized training on lifestyle modification and risk factor management through the residency program. Pharmacists will review participants' medications and may make adjustments according to a medication protocol (Figure 2) for blood pressure, glucose, and lipid control according to the latest evidence-based practice guidelines. Specifically, the medication protocol specifies blood pressure control according to the protocol employed by Kaiser Permanente Health (24), consideration of SGLT-2 inhibitor initiation in patients with diabetes per ACC/AHA and American Diabetes Association (ADA) guidelines (5, 25), and statin initiation or intensification per the 2018 ACC/AHA cholesterol guideline (20). Pharmacists will additionally counsel patients regarding heart-healthy lifestyles and may order laboratory tests when medications are added to follow potassium levels, kidney function, or other relevant laboratory parameters according to the standard of care. Adherence to follow-up lab tests is monitored by the pharmacists, with reminders sent at their discretion according to their typical clinical practice. The study population comprises patients who receive their usual care on the same medical campus as the study site, mitigating access to care limitations for the purposes of this pilot study. The pharmacist visits are provided at no cost to participants; medications are e-prescribed to participants' preferred pharmacies according to the standard of care and are billed through participants' insurance. The results from participants' BNP, hs-cTn, and echocardiography will be provided to them and their primary care physicians as well as the pharmacist and cardiologist team members. Participants in the intervention arm will receive follow-up from the pharmacist team approximately every 3 months for a period of 1 year. Follow-ups will be clinical telephone visits structured similarly to the baseline visit, with interim review of laboratory values, if applicable, for medication monitoring and titration. The pharmacist team will provide a detailed note in the electronic medical record to the primary care doctor after every clinical encounter.

**Figure 2 F2:**
[figure not shown]
Pharmacist-directed intervention treatment algorithm. The treatment algorithm was derived from professional society guidelines for the primary prevention of cardiovascular disease as well as blood pressure, glucose, and lipid lowering. Special consideration is given to the early initiation of SGLT-2 inhibitors in patients with diabetes, given the evidence supporting their efficacy in heart failure prevention and current guideline recommendations. BP represents blood pressure; ACEi angiotensin converting enzyme inhibitor; ARB angiotensin receptor blocker; CCB calcium channel blocker; SMBG self-monitored blood glucose; eGFR estimated glomerular filtration rate; PCP primary care physician; DM diabetes mellitus; SBP systolic blood pressure; DBP diastolic blood pressure; HTN hypertension.

The participants (and their primary care physicians) who are randomized to usual care will be blinded to their 10-year heart failure risk estimates as well as biomarker and echocardiography results, unless there are critical or alert values from the hs-cTn (i.e. >500 pg/mL) or echocardiography (see Supplementary Methods), in which case their primary care physician will be informed. All patients will be requested to repeat the health and lifestyle questionnaire and schedule an in-person visit at 1-year follow-up. At this visit, all participants will undergo repeat measurement of vital signs and anthropometrics, phlebotomy, and echocardiography. The 1-year follow-up time was selected based on a limited duration by which a significant change in risk factor control would be expected based on prior studies (11, 13, 18). Participants receive free parking for all study-related visits and are paid $25 at the end of the study for their time spent participating.

Study data will be collected and managed using REDCap (Research Electronic Data Capture) electronic data capture tools hosted at Northwestern University (26, 27). REDCap is a secure, web-based software platform designed to support data capture for research studies, providing (1) an intuitive interface for validated data capture; (2) audit trails for tracking data manipulation and export procedures; (3) automated export procedures for seamless data downloads to common statistical packages; and (4) procedures for data integration and interoperability with external sources.

### Outcomes

The primary outcome is change in BNP at 1 year. Secondary outcomes include change in hs-cTn, systolic and diastolic blood pressure, weight and body mass index, serum glucose and low density lipoprotein cholesterol, estimated glomerular filtration rate and creatinine, and current smoking at 1 year. Exploratory outcomes include medication adherence and changes in echocardiographic parameters such as left ventricular mass index, diet and physical activity, and health utility at 1 year. Adherence to medications is measured using the same questionnaire as the Atherosclerosis Risk in Communities (ARIC) study: the four-item Morisky Green Levine Scale, frequency of non-adherence in the past 4 weeks, and direct measure of adherence in the past 4 weeks (28). Feasibility will also be examined by monitoring participant retention rates. Retention will be defined as completion of the 1-year study protocol and measured as the proportion of enrolled participants in each arm who successfully complete the study. All demographics (e.g., sex, race, ethnicity, education), health behaviors (e.g., smoking, diet, physical activity), and patient-centered outcomes (e.g., health-related quality of life) are self-reported.

The following serious adverse events will be reported: echocardiogram or troponin alert (at baseline or 1-year follow-up), death, hospitalization, or ER visit (all at 1-year follow-up, or sooner if the study team becomes aware of the adverse event). All adverse events will be determined by chart review and personally adjudicated by the principal investigator. As a process of care intervention using guideline-directed medical therapy (rather than a trial of a novel therapy), drug-related adverse events will not be reported for this study.

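### Baseline alerts are counted as serious adverse events, and events treated outside the health system risk being captured more often in the intervention arm

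*Protocol article*

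**What the plan says.** All of this is in the protocol article.

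- **Event list (Outcomes).** "The following serious adverse events will be reported: echocardiogram or troponin alert (at baseline or 1-year follow-up), death, hospitalization, or ER visit". The alerts thus qualify at either visit.
- **Timing of deaths, admissions and ER visits (Outcomes).** They are captured "all at 1-year follow-up, or sooner if the study team becomes aware of the adverse event".
- **Source and adjudicator (Outcomes).** "All adverse events will be determined by chart review and personally adjudicated by the principal investigator". The same section excludes drug-related adverse events from reporting, so this list is the only adverse-event reporting the article describes.
- **Contact in the intervention arm (Study Protocol).** "Participants in the intervention arm will receive follow-up from the pharmacist team approximately every 3 months for a period of 1 year". These are telephone visits. In addition, "The pharmacist team will provide a detailed note in the electronic medical record to the primary care doctor after every clinical encounter". The first pharmacist visit falls on the day of baseline testing.
- **Contact in usual care (Study Protocol).** No study contact is described between baseline and 1 year. Both arms are then asked to repeat the questionnaire and attend in person.
- **Care setting (Study Protocol).** Participants are described as receiving their usual care on the campus where the study is run.
- **Analysis (Statistical Analysis).** A general chi-square rule covers categorical comparisons between arms. No test of serious adverse events is named.
- **Aim (Discussion).** Safety is one of the things the pilot is expected to inform. The same section concedes that the intervention arm will probably have more contact with the health system.

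**The concern.** Two features of the event definition can affect how counts by arm are read.

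First, an alert on the baseline blood sample or echocardiogram describes the participant's condition before the intervention could have acted. It is a yield of screening, not a consequence of the strategy under test. If it sits in the same count as later events, it adds a similar number to both arms in expectation and pulls any ratio towards 1.

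Second, a chart can show only what has been entered in it. An ER visit at another hospital may be mentioned in a quarterly pharmacist call and so enter the record. The same visit by a usual-care participant has no comparable study route into the record before 1 year. The provision for events known "or sooner if the study team becomes aware of the adverse event" is also easier to meet in the arm that is telephoned.

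At stake is the safety information the pilot hands to the larger trial. Even without a planned test, readers will compare event counts between two arms of 50.

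**Working it through.** **Figures in the plan.** There is nothing to reproduce: the article gives no event rate, alert rate or power for serious adverse events. Its only power statement concerns BNP and does not enter here. The one input taken from the document is 50 per arm; every rate below is an assumption.

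**1. Which events are exposed to unequal capture**

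| Event | Depends on pharmacist contact? |
|---|---|
| Alerts at baseline or 1 year | No: same tests, same visits in both arms (apart from unequal attendance at 1 year) |
| Death | Largely no |
| Admission or ER visit inside the system | Largely no: the 1-year chart review should find it in either arm |
| Admission or ER visit outside the system | Yes, if it is mentioned in a call and noted |

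Only the last row carries the concern.

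**2. Size of unequal capture**

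Let *p* be the true risk, equal in both arms, *f* the share of events outside the system, and *c* the share of those that reach the chart. In-system events are taken as fully captured.

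Recorded risk = *p* × [(1 − *f*) + *f* × *c*]

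Assume *p* = 20%, with *c* = 80% in the intervention arm and 20% in usual care.

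- *f* = 30%: intervention 0.20 × (0.70 + 0.24) = 18.8%; usual care 0.20 × (0.70 + 0.06) = 15.2%. Ratio 18.8/15.2 = 1.24. At 50 per arm: 9.4 versus 7.6 expected participants, a gap of 1.8.
- *f* = 10%: intervention 0.20 × (0.90 + 0.08) = 19.6%; usual care 0.20 × (0.90 + 0.02) = 18.4%. Ratio 19.6/18.4 = 1.07. At 50 per arm: 9.8 versus 9.2, a gap of 0.6.

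The ratio does not depend on *p*; the gap in participants does.

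For scale, the standard error of the larger difference is √[(0.188 × 0.812 + 0.152 × 0.848)/50] = 7.5 percentage points, against a spurious difference of 3.6 points.

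A second calculation sets overall capture directly and enumerates the two-sided 5% chi-square test exactly at 50 per arm, for true risks of 10% to 30%:

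| Capture, intervention vs usual care | Spurious risk ratio | Chance of a significant result |
|---|---|---|
| 100% vs 100% | 1.00 | 5.0% to 5.2% |
| 100% vs 90% | 1.11 | 5.3% to 6.3% |
| 100% vs 80% | 1.25 | 6.2% to 10.4% |
| 95% vs 70% | 1.36 | 6.9% to 14.0% |

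**3. Size of dilution by baseline alerts**

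Let *b* be the share of participants with a baseline alert, the same in both arms and independent of later events. The pooled risk is *b* + (1 − *b*) × *p*. Assume true post-baseline risks of 10% (intervention) and 20% (usual care).

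| *b* | Pooled risks | Risk ratio | Difference (points) | Power at 50 per arm |
|---|---|---|---|---|
| 0% | 10.0% vs 20.0% | 0.50 | 10.0 | 28.6% |
| 2% | 11.8% vs 21.6% | 0.55 | 9.8 | 25.7% |
| 5% | 14.5% vs 24.0% | 0.60 | 9.5 | 22.3% |
| 10% | 19.0% vs 28.0% | 0.68 | 9.0 | 18.3% |

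The ratio moves towards 1. Neither arm is favoured.

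**The case against.** A reader might infer that events are in fact detected unequally, that an excess in the intervention arm is built in, and that the event comparison cannot be interpreted. The article does not support this, for several reasons.

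- The written method is the same in both arms: chart review, with 1 year as the common time point. Learning of an event sooner mainly changes when it is known, not whether the later review finds it.
- The calls are described as medication, laboratory and lifestyle visits. Nothing says that pharmacists ask about care elsewhere.
- Participants receive usual care on the same campus and have a primary care physician in the system, which limits outside events. That the chart covers only this system is itself an inference.
- Serious adverse events are to be reported. They are not a primary, secondary or exploratory outcome, and no pooled test of them is named.
- Baseline alerts carry a time label and can be separated, and randomisation balances them in expectation.
- Masking of adjudication and the full questionnaire content may sit in the full protocol, which is not shown.

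Most of this stands, and it narrows the point to outside-system events and to the labelling of baseline alerts. It does not remove it. The campus statement is made about access to care and does not say that emergencies treated elsewhere are captured. The baseline alerts are on the list in the article's own words: "echocardiogram or troponin alert (at baseline or 1-year follow-up". The Discussion acknowledges the imbalance in contact but does not connect it to how events are found.

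**Conclusion.** The point holds in a limited form. Listing baseline alerts as serious adverse events is explicit in the text and mixes pre-intervention findings with later ones. The consequence is dilution, and only if the two are pooled: under assumed risks of 10% versus 20%, a risk ratio of 0.50 becomes 0.55 to 0.68 with baseline alerts in 2% to 10% of participants.

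Unequal capture is a risk created by the design, not an established fact, and it is confined to ER visits and admissions outside the health system. Its size is unknown. Under the 80% versus 20% capture assumption the spurious risk ratio is 1.07 to 1.24, which is small beside chance variation at 50 per arm. It would not make the safety data uninterpretable. The primary BNP result is unaffected.

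No finding is made on masking of the adjudicator, since the full protocol may address it. The correction is still worth making, because it is cheap and the pilot's event counts are meant to inform a larger trial.

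**What to change.** 1. Report baseline echocardiogram and troponin alerts as screening findings. Count only post-baseline events in the by-arm table.
2. Add one item on ER visits and admissions at any facility to the 1-year questionnaire that both arms already complete, unless it is already there. Use it alongside the chart review, which still covers participants who do not return.
3. Base the by-arm counts on these common sources. List events known only through pharmacist contact separately. Do not discard them: a rule that ignored pharmacist notes altogether would lose genuine safety events.
4. Optionally, state whether the adjudicator sees event summaries with the arm removed.

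The cost is one questionnaire item and some wording. Self-report brings some recall error, and participants who do not return at 1 year will have none.
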